### Subsequent visits

There will be safety checks at week 2, week 4, week 14, and week 16. These timepoints coincide with patients receiving levetiracetam 250 mg twice daily or 500 mg twice daily. Should they so wish, some of the visits may be at the patient’s home or remotely by telephone. If any visits are at the patient’s home, then the carer must also be present throughout that visit. If the visit is conducted remotely by telephone, the researcher should complete all assessments that are possible to complete by telephone as per the schedule of assessments.

At weeks 8 and 20, patients and carers will be required to attend the clinical research site for detailed assessments including all of the measures of efficacy performed at baseline as well as detailed reporting of potential side effects. In the event that visits cannot be conducted at the clinical research site, the visits can be conducted remotely by telephone. The visits should still be conducted as per the schedule of assessments and by staff delegated to complete the specified study tasks. Any assessments not completed need to be documented as a protocol deviation. At week 24, there will be a further telephone consultation with patients who have completed the trial.

In brief the visits can be summarised as follows:
Screening visit: patient screened against inclusion/exclusion criteriaBaseline and randomisation visit: eligible patients who consent to participation are evaluated as outlined and randomised to either receive levetiracetam first or placebo first. Baseline data are captured as detailed in baseline assessmentsTelephone call 2 weeks after randomisation: as levetiracetam/placebo is uptitrating, there will be a telephone call at 2 weeks to ensure no adverse effects and document adherence4-week visit when participants in the active arm will have reached levetiracetam 500 mg twice daily.Eight week efficacy visit to evaluate effect of levetiracetam/placebo using all of the measures performed at the baseline visit.12-week crossover visit. Participants who were randomised to levetiracetam will have weaned to nil and start to take placebo and vice versa. Vital signs, adverse effects and adherence will be recorded. The cognitive and neuropsychiatric measures undertaken at baseline will be repeated to ensure no ‘carry over’ effect from patients who received levetiracetam initially.Telephone call 14 weeks after randomisation: as levetiracetam/placebo is uptitrating, there will be a telephone call at 2 weeks to ensure no adverse effects and document adherence16-week visit when participants in the active arm will have reached levetiracetam 500 mg twice daily.20-week efficacy visit (8 weeks after cross over visit) to evaluate effect of levetiracetam/placebo using all of the measures performed at the baseline visit.24-week end-of-study visit, 24 weeks post baseline. At this visit, patients will have weaned from either levetiracetam or placebo completely. Vital signs, medication adherence and adverse effects will be recorded.Telephone call at 28 weeks after randomisation, 4 weeks after weaning from study medication to document any adverse events from medication

Participants can also make unscheduled visits if required. These visits will be triggered by the participant at any stage through the trial should concerns, particularly relating to possible adverse effects, arise. If an unscheduled visit is required, dependent on the reason for the visit, the visit may occur at the clinical research site, at the participant’s home or telephonically.

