Blood samples (10 ml for analysis of full blood count, urea, creatinine, electrolytes, liver function tests, blood glucose) and a standard urinanalysis (30 ml urine) will be collected once, at the screening visit. These samples are collected to ensure that there is no evidence of sub-clinical renal or hepatic impairment that may not have been apparent from review of the notes alone. Samples will be disposed of using the disposal facilities of the recruiting site as per standard clinical care. The blood and urine samples are only provided to confirm eligibility and will not be retained.

Randomisation will occur at or shortly after the baseline visit. Levetiracetam and placebo will be packaged with clear instructions to take tablets as outlined (Table 2; Fig. 3). Each tablet of levetiracetam is 250 mg. Participants will commence on one tablet at night and increase by one tablet every week to two tablets twice daily (Table 2; Fig. 3). They will then continue on two tablets twice daily for 4 weeks before reducing by one tablet each week until the IMP is withdrawn. The participant will then cross over to either levetiracetam or placebo, whichever they were not initially allocated to, and complete the same up- and down-titration schedule. Given the short half-life of levetiracetam (6 to 8 h (SMPC)) and the assessment schedule, which includes repeat testing prior to entry into the second arm of the trial, a washout period after the first arm was not thought necessary.

**Table 2 Tab2:** Planned titration regime of IMP during ILiAD study

	Daily morning dose (each tablet 250 mg)	Daily evening dose (each tablet 250 mg)
**Week 1**	Nil	One tablet
**Week 2**	One tablet	One tablet
**Week 3**	One tablet	Two tablets
**Week 4**	Two tablets	Two tablets
**Week 5**	Two tablets	Two tablets
**Week 6**	Two tablets	Two tablets
**Week 7**	Two tablets	Two tablets
**Week 8**	Two tablets	Two tablets
**Week 9**	One tablet	Two tablets
**Week 10**	One tablet	One tablet
**Week 11**	Nil	One tablet
**Week 12**	Nil	Nil

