### Sample size {14}

The trial is relatively short and one would not anticipate being able to detect changes in ADAS-Cog over this time-frame. Therefore, the trial is powered to detect a standardised effect of 0.7 in a specific and sensitive test of hippocampal function that has already been tested in people with AD [24, 25]. The estimated variability of 2% was taken from data on a memory-binding task for older individuals (aged 60–83) [26]. The standard deviation of the difference between the treatment and placebo was then calculated assuming equal variability in the two groups. This yielded an estimate of 3%. Using the two-sided test for paired means in PASS 11, the total sample required to detect a mean difference of 2.1% with a standard deviation of the difference of 3% and achieve 90% power at a 5% significance level in 24 patients.

Therefore, a sample size of 30 allows an attrition rate of 20% for the study still to be able to detect a meaningful difference in sensitive measures of cognitive function.

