## Statistical methods

### Statistical methods for primary and secondary outcomes {20a}

A trial-specific statistician based at the Centre for Statistics in Medicine, University of Oxford, will perform statistical analysis.

As the trial is crossover in design, all analyses will be within participants, comparing outcome measures after taking the placebo and after taking levetiracetam. Thus, the analyses of the primary and secondary outcomes relating to cognition, behaviour and quality of life will be based on the differences between the observations at the efficacy visits (week 8 and week 20) of the levetiracetam and placebo periods.

Within a given patient, levetiracetam and placebo will be compared using the paired t-test and the analysis of covariance adjusting for baseline values. We will compare results at 8 weeks to the initial baseline testing and at 20 weeks to the further baseline testing at 12 weeks. All results will be presented with 95% confidence intervals. For each carer who has consented to provide data, quality of life measures will likewise be compared between the observations at the week 8 and week 20 visits. Appropriate sensitivity analyses will be performed to confirm the robustness of the data.

EEG will be computationally analysed, after standard cleaning, downsampling and artefact rejection. Typical EEG data features of interest include time series measures (for example, mean, variance, skewness, kurtosis and coastline), frequency based features (e.g. band-passed power and rhythmicity) and channel pair-wise bivariate connectivity metrics. These baseline EEG features will be correlated with clinical outcome measures.

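### Two non-equivalent primary contrasts are described; the one using the week-12 value as baseline is open to carry-over bias, is not the one powered, and the week-12 retest cannot rule that bias out

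*Protocol article*

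**What the plan says.** Outcomes {12}, Primary, defines the measure as change within each arm: end of arm 1 against baseline, and end of arm 2 against the start of arm 2. The start of arm 2 is the week-12 crossover visit.

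Statistical methods {20a} first bases all cognitive, behavioural and quality-of-life analyses on the difference between the two efficacy visits, week 8 and week 20. It then names a paired t-test and an ANCOVA adjusting for baseline, and adds that results will be compared at 8 weeks with the initial baseline and "at 20 weeks to the further baseline testing at 12 weeks". No order of priority is given.

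On carry-over, the visit list under Subsequent visits says of week 12: "The cognitive and neuropsychiatric measures undertaken at baseline will be repeated to ensure no" carry-over in those given levetiracetam first. Intervention description {11a} gives two reasons why "a washout period after the first arm was not thought necessary": the 6 to 8 h half-life, and the repeat testing before arm 2. Table 2 shows no tablets in week 12.

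**The concern.** The same week-12 measurement is meant to check for carry-over and also, in one of the two descriptions, serves as the baseline subtracted from week 20. If levetiracetam-first participants still differ at week 12 because of earlier treatment, the difference enters the raw change contrast. A residual benefit that then fades makes the placebo period look like a decline and inflates the drug effect. A withdrawal effect works in the opposite direction.

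Two things are at stake: which estimate is the trial's primary result, and whether the stated 90% power belongs to it. The retest offers reassurance only if it is precise enough to exclude a carry-over that matters against a 2.1-point target.

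**Working it through.** **Inputs** (Sample size {14} unless noted)
- Target difference 2.1%; SD of the treatment–placebo difference 3%; two-sided 5%.
- Single-measurement SD 2%: "The estimated variability of 2% was taken from data on a memory-binding task for older individuals".
- 30 recruited, 15 per sequence (Intervention description {11a}); at least 24 completers (section {11b}), so about 12 per sequence.

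**1. The plan's own figure.** For a paired t-test the normal approximation gives ((1.960 + 1.282) × 3/2.1)² = 21.4. Exact noncentral-t power is 87.9% at n = 22, 89.4% at 23 and 90.7% at 24. This reproduces "achieve 90% power at a 5% significance level in 24 patients", and 24/0.8 = 30. The SD is explained by "The standard deviation of the difference between the treatment and placebo was then calculated assuming equal variability in the two groups": √2 × 2% = 2.83%, rounded up to 3%. That is a difference of two measurements with zero correlation, so the powered contrast is week 8 versus week 20.

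**2. SD and power of raw change.** Let each visit have variance σ² and every pair of visits correlation ρ.
- Y8 − Y20: variance 2σ²(1 − ρ).
- (Y8 − Y0) − (Y20 − Y12): variance 4σ²(1 − ρ).

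The SD rises by √2 whatever ρ is. From 3% it becomes 4.24%, with noncentrality 2.1/4.24 × √24 = 2.42 and power 64%. From 2.83% it becomes 4.00%, with noncentrality 2.57 and power 69%.

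**3. Bias.** Let τ be the treatment effect, c the carry-over at week 12 in the levetiracetam-first sequence, and f the fraction left at week 20. Expected values at weeks 0, 8, 12 and 20 are 0, τ, c, fc (levetiracetam first) and 0, 0, 0, τ (placebo first).
- Raw change, levetiracetam minus placebo: τ + c(1 − f) and τ. The average is τ + c(1 − f)/2.
- Week 8 versus week 20: τ − fc and τ. The average is τ − fc/2.

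For an illustrative c = 1.05 (half the target):

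| f | Raw-change bias | Week 8 v 20 bias |
|---|---|---|
| 0 | +0.53 | 0 |
| 0.5 | +0.26 | −0.26 |
| 1 | 0 | −0.53 |

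A practice effect common to both sequences cancels when the sequences are equal in size. Only a sequence-specific effect matters here.

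**4. ANCOVA.** Regress the treatment difference on the baseline difference. With equal correlations, cov(Y8 − Y20, Y0 − Y12) = σ²(ρ − ρ − ρ + ρ) = 0, so the fitted slope is near zero and the bias is about 0. With correlations that decline over time, simulation at c = 1.05 and f = 0 gives a bias of 0 to about 0.2, against about 0.5 for raw change.

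**5. What the retest can show.** The article names no comparison, so a between-sequence t-test on week-12 scores is assumed.
- 12 versus 12, SD 2%: SE = 2 × √(2/12) = 0.816; half-width 2.074 × 0.816 = 1.69. Power is 69% for c = 2.1 and 23% for c = 1.05.
- 15 versus 15: half-width 1.50; power 79% and 28%.
- 12 versus 12 with baseline adjustment, assumed correlation 0.5 to 0.7 (residual SD 1.73 to 1.43): half-width 1.46 to 1.21.
- 12 versus 12 on unadjusted change from baseline (SD 2.83 to 3): half-width 2.40 to 2.54.
- Week 12 against baseline within 12 levetiracetam-first participants (SD 3%): half-width 1.91, confounded with practice and progression.

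A carry-over of 1.69 is compatible with an observed sequence difference of zero. If it had faded by week 20, it would bias raw change by 0.85 points, 40% of the target.

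**6. Residual drug.** One nil-dose week is 168 h: 168/8 = 21 to 168/6 = 28 half-lives.

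**The case against.** The article often uses *ensure* to mean *check*: the week-2 call and the screening samples are described the same way, and none of these claims statistical proof. A reader might infer that the plan will take a non-significant week-12 test as proof of no carry-over. The document does not say so. It states no test and no such decision rule, and these could properly sit in the analysis plan. This stands, and the point does not rest on that reading.

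A reader might also infer that the absence of a washout rests on the retest. It does not rest on that alone. The half-life is the first reason given, and with the nil-dose week it makes residual drug implausible. Nothing in the document shows a carry-over of 1 to 2 points. The sizes above are illustrations of what the retest could miss, not expectations.

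The c/2 figure holds only for raw change scores and an effect gone by week 20. The ANCOVA in {20a} largely escapes it, and the paired week 8 versus week 20 difference, already in {20a}, escapes it entirely when f = 0. This also stands. It is why the remedy is to give that contrast priority, not to introduce something new.

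What the objection does not remove is the definition in Outcomes {12}, repeated in the comparison with week 12 in {20a}. As written, raw change from week 12 remains a candidate for the primary result.

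**Conclusion.** The point holds as an unresolved choice between two contrasts that differ in bias and precision. On the plan's own SDs and equal correlations among visits, raw change from week 12 has about 64% to 69% power at 24 patients, against 90.7% for week 8 versus week 20. It also carries a bias of c(1 − f)/2. The retest cannot exclude a c that matters: half-width 1.7 points at 12 versus 12, 1.5 at 15 versus 15.

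The power figures depend on the plan's implicit zero correlation. At a correlation of 0.5 the raw-change SD would be 2 × √(4 × 0.5) = 2.83% and its power 94%. The √2 penalty relative to week 8 versus week 20 would remain. If the 2% SD, taken from older individuals, is too small for Alzheimer's disease, power falls and the retest becomes less precise.

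The documents do not support the stronger conclusions that carry-over is likely, that the primary estimate is biased, or that the schedule needs a washout. Any effect at issue would be pharmacodynamic, a withdrawal effect, or learning that differs by sequence.

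**What to change.** 1. In Outcomes {12} and Statistical methods {20a}, name the within-participant week 8 versus week 20 difference, with a period term, as the single primary contrast. This matches the contrast that the sample size is based on.
2. Keep the analysis using the week-12 baseline as a sensitivity analysis, fitted as ANCOVA and not as raw change.
3. Under Subsequent visits, replace *ensure no* with *estimate, with 95% CI, any* before the carry-over effect. State that the choice of analysis will not depend on the result.

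The cost is wording only; no visit, dose or schedule changes. Two downsides should be stated. If a carry-over persisted fully to week 20, the week 8 versus week 20 contrast would be biased by c/2 (toward the null for a residual benefit), whereas raw change would be unbiased. Any precision gained from adjusting for week 12 is also given up in the main model; under equal correlations that gain is nil (step 4).

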### Strategies to improve adherence to interventions {11c}

To improve adherence to medication the carer of the patient will be given a tablet chart (Fig. 3) to help the accurate administration of medication. Tablets will be counted on return, which will further clarify concordance with the planned dosing. The involvement of the carer will also help ensure concordance with other aspects of the study.

### Relevant concomitant care permitted or prohibited during the trial {11d}

Levetiracetam does not interact pharmacokinetically with many other medications. Should acute treatments be needed, for example a course of antibiotics, the participant will continue in the trial. A file note will be made of the start date and end date of any such treatments. Participants must not be involved in other clinical trials while recruited to ILiAD.

### Definition of end of trial

The end of trial is the date of the last telephone follow-up of the last participant.

### Provisions for post-trial care {30}

The trial does not progress to an open label extension study. Were the trial to yield promising data, then a much larger study to thoroughly evaluate the efficacy of levetiracetam in this participant group will be performed. The University of Oxford has a specialist insurance policy in place which would operate in the event of any participant suffering harm as a result of their involvement in the research. NHS indemnity operates in respect of the clinical treatment that is provided.

### Outcomes {12}

#### Primary

Changes in cognition in patients while taking levetiracetam as measured by computerised assessment of hippocampal binding memory task. Measures will be compared as change from baseline in each arm of the study (namely compare end of arm 1 to baseline and end of arm 2 to measures taken at start of arm 2). Were the study to show that levetiracetam can stabilise or even improve cognitive testing on a very specific task that evaluates hippocampal function that would open an entirely new therapeutic avenue for people with Alzheimer’s disease.

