## Interventions

### Explanation for the choice of comparators {6b}

We would not expect to see major changes in Alzheimer’s Disease Assessment Scale–Cognitive Subscale (ADAS-Cog, a standard measure of cognition applied in AD research) over 24 weeks. Therefore, more sensitive markers of cognition will be employed including a neuropsychological test measuring binding of features which has been shown to be important in memory associated with hippocampal function [24], including in familial AD [25]. We have accounted for a possible attrition of 20% and a cohort of 30 participants is adequately powered to detect a meaningful difference of 0.7 in the hippocampus-dependent memory-binding test. Standardised and widely deployed scales to measure quality of life and psychological/psychosocial factors will also be utilised

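### The stated 90% power is for the direct levetiracetam–placebo difference at the efficacy visits, not for the difference of two changes from baseline that defines the primary outcome

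*Protocol article*

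**What the plan says.** Four places in the protocol article bear on the primary comparison.

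- **Outcomes {12}, Primary.** "Measures will be compared as change from baseline in each arm of the study". Each arm has its own baseline: the end of arm 1 is set against the study baseline, and the end of arm 2 against the start of arm 2.
- **Sample size {14}.** A variability of 2%, from older people doing a memory-binding task, is turned into an SD of 3% for the treatment–placebo difference, assuming equal variability in the two groups. "Using the two-sided test for paired means in PASS 11", the plan sets out to "detect a mean difference of 2.1% with a standard deviation of the difference of 3" per cent and "achieve 90% power at a 5% significance level in 24 patients". Thirty are recruited to allow for 20% attrition.
- **Statistical methods {20a}.** The cognitive analyses "will be based on the differences between the observations at the efficacy visits (week 8 and week 20"), which is the direct comparison. The next paragraph says that "levetiracetam and placebo will be compared using the paired t-test and the analysis of covariance adjusting for baseline values", and then that week 8 is compared with the initial baseline and week 20 with the week-12 testing, which is the change-score comparison again.
- **Choice of comparators {6b}.** "a cohort of 30 participants is adequately powered to detect a meaningful difference of 0.7 in the hippocampus-dependent memory-binding test". Sample size {14} shows that 0.7 is the standardised effect, 2.1/3.

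**The concern.** The sample size rests on the spread of a difference between two scores per participant. The primary outcome as defined is a difference between two changes, so it carries the noise of four scores. Unless the extra two scores are well correlated with the efficacy scores, subtracting them adds more variance than it removes, and the quoted power does not apply.

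This trial is meant to decide whether a larger study follows. If the change score is analysed as primary, a null result would be read as coming from a test with a 10% chance of missing a 2.1-point effect, when that chance could be 31% to 36%. Because {12} and {20a} describe two different contrasts, a reader also cannot tell which one the 90% describes.

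**Working it through.** **Inputs.** All are from Sample size {14}: mean difference 2.1%, single-score variability 2% (taken as an SD), SD of the difference 3%, two-sided 5%, 24 completers. The contrasts come from {12} and {20a}. Power is exact for the paired t-test (noncentral t, n − 1 degrees of freedom, noncentrality √n × 2.1/SD).

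**1. The plan's own figure.** √2 × 2% = 2.83%, given as 3%. This step fits a two-score difference with no within-participant correlation. The standardised effect is 2.1/3 = 0.7. At n = 24 power is 90.7% and at n = 23 it is 89.4%, so 24 is the smallest n for 90%. Then 24/0.8 = 30. The figure reproduces.

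**2. SD of the change-score contrast.** Let E be the levetiracetam-minus-placebo difference at the efficacy visits and B the same difference at the two period baselines. The direct contrast is E, and the change-score contrast is E − B. If E and B each have SD S, and r is their correlation:

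Var(E − B) = S² + S² − 2rS² = 2S²(1 − r).

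With no carry-over B has mean zero, so the expected effect stays at 2.1.

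If all four visits share a common correlation ρ and score SD s, then r = 0, Var(E) = 2s²(1 − ρ) and Var(E − B) = 4s²(1 − ρ). The variance is doubled whatever ρ is. Zero correlation, which the step from 2% to about 3% implies, is one such case.

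**3. Power at r = 0.**

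| Direct SD (S) | Change-contrast SD (√2 × S) | Power, n = 24 | Power, n = 30 | Completers for 90% |
|---|---|---|---|---|
| 2.83% (unrounded) | 4.00% | 69.3% | 79.4% | 41 |
| 3% (as planned) | 4.24% | 64.2% | 74.6% | 45 |

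**4. Sensitivity to r** (assumed values; the protocol gives none), n = 24.

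| r | Change contrast, S = 2.83% | Change contrast, S = 3% |
|---|---|---|
| 0 | 69% | 64% |
| 0.2 | 79% | 74% |
| 0.3 | 84% | 79% |
| 0.4 | 89% | 85% |
| 0.5 | 94% | 91% |

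The change contrast has an SD of exactly 3%, and so 90.7% power, when 2S²(1 − r) = 9. That gives r = 1 − 9/16 = 0.44 for S = 2.83% and r = 1 − 9/18 = 0.5 for S = 3%.

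**5. Baseline-adjusted alternative.** Regressing E on B leaves a residual SD of S√(1 − r²), never above S. With S = 3% that is 3.00% at r = 0, 2.86% at r = 0.3 and 2.60% at r = 0.5. Power at n = 24 is then about 91%, 93% and 97%, and allowing one degree of freedom for the covariate changes these by about 0.1 point.

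**The case against.** The strongest reply is that the 90% does belong to an analysis in the plan. Statistical methods {20a} opens with the direct week-8 versus week-20 difference and adds a baseline-adjusted analysis, and the stated power holds for both. An analysis plan that is not shown may also rank the two tests. This stands, and it limits the point to an inconsistency: the sample-size arithmetic is not wrong. It does not remove the point, because {12} states the change score as the primary outcome and {20a} repeats it. An analysis plan could choose one contrast only by departing from {12} or from the basis of {14}.

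A second reply is that the protocol states no correlation, so 64% to 69% is one case and not a result. That also stands. A reader might infer that the trial simply has 64% to 69% power; the documents do not support this. The figures need r = 0 and 24 completers, and section {11b} aims for 30 completers, with 24 as the minimum. The lower figure also carries forward the rounding of 2.83% to 3%. Nor must every pair of visits be correlated for the change score to recover. With s = 2%, a correlation of 0.4375 within each period and none between periods, each change has variance 2 × 4 × 0.5625 = 4.5, and the contrast has variance 9 and SD 3%. A common correlation of that size with s kept at 2% also gives 3%, although the direct SD would then fall to about 2.1%, not the planned 3%.

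Two further readings are tempting and are not supported:

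- **Carry-over into the week-12 baseline.** The protocol reports a half-life of 6 to 8 h, tapers the drug, has a nil-dose week 12, and repeats testing then to check for carry-over. No residual effect is shown.
- **A planning SD too small for Alzheimer's disease.** The 2% does come from older people, as the protocol openly says, but it gives no figure for patients, and the cited data are not available here.

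**Conclusion.** The point holds as a mismatch between the primary outcome and the sample size. The 90% (recomputed 90.7%) applies to the direct week-8 versus week-20 difference, and at least as well to its baseline-adjusted form. It does not apply without qualification to the difference of two changes. With the direct SD held at the plan's value and r = 0, that contrast has about 64% to 69% power with 24 completers and 75% to 79% with 30. It reaches 90% with 24 completers only at r of about 0.44 to 0.5. These figures assume no carry-over and equal variance of the baseline and efficacy-visit differences. The 0.7 in {6b} is a separate, small misstatement of scale.

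**What to change.** 1. In {12}, {14} and {20a}, name one primary contrast: the within-participant levetiracetam-minus-placebo difference between the efficacy visits (week 8 and week 20), with the period-baseline difference as a covariate. On the stated SD, power is about 90% or more.
2. Keep the change-from-period-baseline comparison as supportive.
3. If change scores are to remain primary, replace the single 90% in {14} with a range tied to a stated and justified correlation between the period-baseline and efficacy-visit differences. At r = 0, 90% power would take 41 to 45 completers, or 52 to 57 recruited at 20% attrition (41/0.8 = 51.25; 45/0.8 = 56.25).
4. In {6b}, state 0.7 as a standardised effect, equal to 2.1 percentage points.

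Items 1, 2 and 4 change wording only and need no extra participants, visits or data. Item 3 would lower the stated power or raise the sample size, unless the correlation can be supported.
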